## **2.2. Outcomes**

### Primary Outcomes

- a. Medication tolerability
  - i. Study withdrawal due to medication side effect (subjective or lab criteria)
  - ii. Discontinuation of a single study medication due to side effect (subjective or lab criteria)
  - iii. Lab measure with  $> 2$  fold increase (with emphasis on: Creatinine, CK, AST, ALT)
- b. Adherence to study medication
  - i. Self report of misses per week
  - ii. Pill count by study RN – reported as % (pills taken/days enrolled in study)
- c. Changes in Framingham risk score (FRS), including serum cholesterol levels and blood pressure

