#### Study Drug:

The choice of drugs for this study was motivated by their efficacy as secondary prevention for CVD events, adjunct anti-inflammatory properties, availability as generic preparations, and potential to counter HIV- and ART-specific CVD risk mechanisms beyond BP and lipid lowering properties. In addition, some statin medications are contraindicated when taking PIs (due to interactions with CYP3A4 pathway), and for this reason pravastatin is the preferred given a lack of metabolism through the CYP3A4 pathway. Darunavir has been noted to increase pravastatin levels to a greater extent than other PIs, and participants taking darunavir will be counseled specifically about this but will not be excluded from participating for this reason.

Both pravastatin and lisinopril are available in generic form. These drugs also have a long track record of being used safely in a clinical setting. Participants for whom BP or cholesterol treatment is indicated will not be enrolled. In addition to clinical monitoring for side effects, toxicity labs will be included at study visit. A clinical doctor of pharmacy (PharmD) is included on the protocol team and will review each participant's medication list upon enrollment. If toxicity to study drugs develop, then participants will be un-blinded and discontinue any active study medication per monitoring criteria below.

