## **2.4. Data Collection**

Details of study will be reviewed with all interested participants. If inclusion criteria are likely based on review of clinic records then a screening visit may be scheduled, where labs and BP will be assessed. Informed consent will be obtained at screening visits. Screening blood draw results will be used to verify blood lipid eligibility criteria (LDLc and TG). The lowest BP reading, taken from up to 3 readings during a screening visit, may be used to assess eligibility criteria. Participants will be given an information pamphlet on ways to reduce heart disease risk at enrollment. If exclusion or withdrawal criteria are met due to BP or lipid level thresholds, then a note with these results will be sent to the participants primary care giver with recommendations that they be evaluated for hypertension or dyslipidemia, respectively.

If eligibility criteria are met, participants will be randomized at the baseline visit to occur within 2 months of screening/consent. After enrollment and baseline visit, participants will present month 1 and month 4 for repeat study procedures. The visit schedule is outlined in the table below. Visits will last approximately 60 minutes.

Toxicity labs and a clinical assessment will be scheduled at any point during the 4 months follow-up if new symptoms develop that may be related to study medications. Toxicity labs and adherence will otherwise be assessed along with study procedures at scheduled 1 and 4 month visits.

**TABLE:** Study procedures and visit timeline

| Measure                      | Screening visit            | Baseline visit       | Symptoms? | Month 1 visit | Month 4 visit |
|------------------------------|----------------------------|----------------------|-----------|---------------|---------------|
| Informed consent             | X                          |                      |           |               |               |
| Randomization                |                            | X                    |           |               |               |
| BP                           | X                          | X                    |           | X             | X             |
| Lipids (TC, HDLc, LDLc, TG)  | X                          | X (if not at screen) |           | X             | X             |
| FRS                          | X                          | X                    |           | X             | X             |

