| Med Adherence                |                            |                      | X         | X             | X             |
| Hep B/C serologies           | X                          | X (if not at screen) |           |               |               |
| Toxicity labs (CMP, CBC, CK) | X                          | X (if not at screen) | X         | X             | X             |
| HIV labs (RNA, CD4)          | X (if not $\leq 3$ months) | X (if not at screen) |           | X             | X             |
| Artery Elasticity            |                            | X                    |           | X             | X             |
| Biomarkers                   |                            | X                    |           | X             | X             |
| Stored Specimens             |                            | X                    |           | X             | X             |

Randomization will be predetermined using block-randomization with varied groups of 4 and 8, and blinded to investigators, staff and participants. An un-blinded statistician, one research staff not involved with study visits, and an HCMC pharmacist will have access to the randomization code.

Pravastatin and lisinopril will be purchased through HCMC pharmacy at reduced generic pricing. Active study drugs and placebo pills will be encapsulated (Custom-Rx Compounding Pharmacy in Richfield, MN) and then packaged and labeled with a study identification number. Study medications will be stored and dispensed by study investigators. Investigators will comply with HCMC policies on use of medications for ongoing IRB approved studies.

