### 3.2. Participant Safety Monitoring and Withdrawal

Participants will undergo clinical assessment for side effects to study medication at baseline and each follow-up visit (months 1 and 4). Toxicity labs will be assessed per 2.6 above at each study visit, or at any point during the study if symptoms suggestive of drug toxicity/intolerance develop. A clinical pharmacist will participate on protocol team (i.e., [name]) and will review the active clinical medication list upon request for participants prior to enrollment – where potential drug-drug interactions will be identified. Participants taking darunavir (which may increase pravastatin levels to a greater extent than other PIs) will not be excluded from participating from the study, but if a trend is suspected toward more toxicity in these participants then darunavir use may be added to exclusion criteria. Participants may withdraw from the study at any time at their request, as described in the consent.

Participants will be un-blinded to study medication (and will stop any active drug) if toxicity is clinically suspected, or if any of the following criteria are met:

- i. ALT/AST levels double from baseline, increase to  $\geq 10$  x upper limit of normal, or any elevation associated with clinical symptoms.
- ii. CK increase to an absolute level of  $>4$ x upper limit of normal
- iii. Serum creatinine increase  $>0.5$  mg/dL and to an absolute level  $>2.0$  mg/dL; if only one of these criteria are met toxicity labs will be repeated in 2 weeks.
- iv. Blood pressure  $>140/90$ mmHg at baseline and month 1 (lowest value may be used at each visit), when a participant fulfilled the BP thresholds/requirements at screening visit
- v. New clinical indication for ACEi or statin medication that was not present at enrollment

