## 4. ANALYSIS PLAN

The general goal of this pilot study is to gather feasibility and efficacy data, utilizing a 2x2 factorial design (4 cells of  $n=10$ ,  $n=40$  total), to inform planning for a multi-center HIV/CVD polypill trial. We believe treatment with pravastatin (20mg daily) and lisinopril (10mg daily) will be well tolerated and be well adhered to by participants engaged in care and already adherent to ART. We hypothesize that Framingham risk score will improve with either drug intervention. Future sample size estimates will be generated from effect size related to changes in arterial elasticity and biomarkers.

**Primary Analyses:** Mean changes in FRS after 4 months will be studied with pravastatin use (versus placebo) and lisinopril use (versus placebo). The effect of both drugs combined, compared with double-placebo, will also be examined. Adherence and the frequency of intolerability, based on subjective or lab criteria, will also be compared between groups using the definitions listed in ‘outcomes’ (2.2). Elevations in lab values will also be categorized by severity (using established grades 1-4).

**Secondary Analyses:** Mean changes in hsCRP, IL-6, D-dimer, SAE, ApoB, ApoA1, and LDL and HDL particle concentrations will be studied after 4 months of pravastatin and lisinopril, given alone or in combination, using similar methods as above in primary analyses. Tests for correlation between change in these markers and BP, total cholesterol and FRS will also be considered. Regression models may be

considered to adjust for additional clinical characteristics (including, but not limited to traditional CVD risk factors), but power will be quite limited for these analyses.

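### Suspected toxicity opens the code and stops only active drug, so on the natural reading a rule-driven stop under primary outcome a.ii can arise for an active capsule but not for a placebo capsule (minor)

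*Combined protocol and SAP*

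**What the plan says.** Section 3.2 (Participant Safety Monitoring and Withdrawal) sets the response to suspected toxicity or to any of five listed criteria: "Participants will be un-blinded to study medication (and will stop any active drug) if toxicity is clinically suspected". Section 2.3 (Study Drug) repeats the order: "participants will be un-blinded and discontinue any active study medication per monitoring criteria below". Section 2.4 sets active drugs against placebo pills when it describes encapsulation. For study capsules, therefore, active means not placebo.

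Section 2.2 lists tolerability as the first primary outcome. Item a.ii is "Discontinuation of a single study medication due to side effect (subjective or lab criteria"), and item a.iii is a more than 2-fold laboratory rise. Section 4 says: "Adherence and the frequency of intolerability, based on subjective or lab criteria, will also be compared between groups", using the section 2.2 definitions. It also grades laboratory elevations 1-4.

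Triggers are not confined to laboratory results at scheduled visits. Section 2.4 provides: "Toxicity labs and a clinical assessment will be scheduled at any point during the 4 months follow-up if new symptoms develop". Criterion i in section 3.2 includes "any elevation associated with clinical symptoms".

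The plan does not say that a placebo capsule is stopped after a trigger, that the trigger is recorded as an outcome before unblinding, whether a.ii is counted per capsule or per participant, or how stopping both drugs is classified.

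**The concern.** A placebo group shows how often symptoms and chance laboratory rises would lead to stopping a capsule when no drug is responsible. That works only if the same event is counted the same way in each group. Here the trigger is judged blind, but the action that a.ii counts is chosen after the code is opened and depends on what the capsule contains. Background events can then enter a.ii on active drug and drop out on placebo.

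At stake is the first-listed primary outcome, and the first study hypothesis, of a pilot meant to inform a multi-center polypill trial. With 20 v 20 for each drug, one or two such stops could make up much of what a.ii shows. If stops of both drugs are not counted as stopping a single medication, the combination cell, which is the polypill itself, contributes no rule-driven stops.

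**Working it through.** The plan gives no figure for a.ii, so there is none to reproduce. The 80% power in section 2.5 concerns the Framingham score and does not bear on this point.

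**Inputs.** There are 4 cells of 10 (section 4), hence 20 v 20 for each drug (section 2.5). Let q be the chance that a participant has a toxicity trigger unrelated to drug, equal in all cells. The documents give no q; 5-10% is assumed. Only clinical suspicion and criteria i-iii count, because iv (blood pressure) and v (a new indication) are not side effects.

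**Rule-driven stops by cell.** After a trigger, each single-active cell stops one drug (10q participants). The double-active cell stops two (10q participants). The double-placebo cell stops none.

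**Expected counts for one drug, active v placebo, each of 20:**

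| How a.ii is counted | Formula | q = 5% | q = 10% | Risk difference |
|---|---|---|---|---|
| Per capsule, double stops left out | 10q v 0 | 0.5 v 0 | 1 v 0 | q/2 = 2.5-5 points |
| Per capsule, double stops included | 20q v 0 | 1 v 0 | 2 v 0 | q = 5-10 points |
| Per participant, double stops left out | 10q v 10q | 0.5 v 0.5 | 1 v 1 | 0 |
| Per participant, double stops included | 20q v 10q | 1 v 0.5 | 2 v 1 | q/2 = 2.5-5 points |
| Trigger counted alike in every arm | 20q v 20q | 1 v 1 | 2 v 2 | 0 |

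In the third row the margins agree only because each side contains one single-active cell. By cell of 10, the expected count is 0.5-1 in each single-active cell, 0 in double placebo and 0 in double active. If double stops are included, double active also has 0.5-1.

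**How often nothing would show.** The chance that a given drug has no rule-driven stop at all is (1-q)^10 = 0.599 and 0.349 at q = 5% and 10% with double stops left out, and (1-q)^20 = 0.358 and 0.122 with them included.

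**Is there an excess of false positives?** The plan names no test. With Fisher's exact test at two-sided 0.05 and no drug effect, the chance of p < 0.05 at q = 5% and 10% is, in table order: 0.0001 and 0.0016; 0.0026 and 0.0432; 0.0001 and 0.0011; 0.0016 and 0.0162; 0.0019 and 0.0118. All are below 0.05.

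**Laboratory part.** As an illustration, the chance that one enzyme doubles from baseline at one visit is 1 - Phi(ln 2 / (s x sqrt 2)), where s is an assumed within-person SD on the log scale. At s = 0.15, 0.20, 0.25 and 0.30 this is 0.05%, 0.71%, 2.5% and 5.1%. For ALT or AST, taken as independent, it is 0.1%, 1.4%, 4.9% and 10.0%. These are one-visit rates, and two follow-up visits are scheduled. Outcome a.iii largely captures such events in every arm, since it covers a rise of more than 2 "fold increase (with emphasis on: Creatinine, CK, AST, ALT").

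**What remains.** The part without that cover is mainly symptom-driven: clinical suspicion at any time in the 4 months, and the symptom clause of criterion i, which can fire below a 2-fold rise. Its rate cannot be estimated from the documents; the formulas apply to any assumed rate.

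**The case against.** The strongest reply is that section 3.2 is a patient-management instruction, not an outcome definition. Item a.ii speaks of a study medication rather than an active drug, so a placebo capsule stopped for side effects would fit it. Section 3.2 also uses active to mean currently taken when it mentions the clinical medication list. This reading is possible. But the contrast in section 2.4, and the fact that the code is opened before the action, favor the other one: unblinding first serves a purpose only if the action depends on content.

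Second, if participants are counted and single is taken literally, neither drug's margin is biased, and double active v double placebo is 0 v 0. This stands, so the size of the bias cannot be stated without naming the counting rule. Even then, a.ii says nothing about rule-driven stops on the combination.

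Third, sections 2.6 and 3.2 have symptoms assessed alike in every arm, and the CRFs are not part of the documents. The blinded event may therefore already be recorded. This also stands; it limits the firm part of the fix to what a.ii counts.

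A reader might infer more: that tolerability cannot be compared at all, or that the rule will produce false-positive findings. The documents support neither. Participants can stop a placebo capsule by choice or withdraw, and a.iii, the laboratory grading and adherence are unaffected. Item a.i would be affected only if stopping all active drug were treated as study withdrawal, which the plan does not say. High Fisher rejection rates (17-76%) appear only at assumed trigger rates of 15-30%, counted per capsule with double stops included. Nothing in the documents supports such rates.

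**Conclusion.** The point holds as a minor defect in a primary outcome. If the stated rule is followed, whether a rule-driven a.ii event exists depends on the randomized content of the capsule. At an assumed background trigger rate of 5-10% and no drug effect, the result is a bias of 2.5-10 points against each drug under three of the four counting rules. Under the fourth, the margins are equal and the double-active and double-placebo cells have no rule-driven stops. In expected numbers, the excess is at most 1-2 stops among 20.

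The conclusion rests on reading active as not placebo, and its size rests on assumed rates. Any bias runs against the drugs, so it would not falsely reassure about tolerability. No decision rule uses a.ii, and section 4 bases future sample sizes on arterial elasticity and biomarkers. Most laboratory triggers are already covered elsewhere; the exposure is mainly in symptom-driven stops.

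**What to change.** For the between-group comparison, define the a.ii event in section 2.2 as a toxicity trigger (clinical suspicion, or criteria i-iii of section 3.2) judged and recorded before the code is opened. Count it once per participant in every arm, whatever the capsules contained, and refer to this definition in section 4. Counting the trigger once per participant also settles the unit and the double-stop question for the comparison. Report actual stops of active drug descriptively by cell, stating there how stopping both drugs is classified.

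Leave unblinding, the stopping of active drug, a.iii and the laboratory grading as they are.

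Blind judgement is feasible because the code is held away from the visits: besides an unblinded statistician, "one research staff not involved with study visits, and an HCMC pharmacist will have access to the randomization code". The cost is one CRF item, if it is not already there, and a re-worded definition. No visits, tests or participants are added.

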## 4. ANALYSIS PLAN

The general goal of this pilot study is to gather feasibility and efficacy data, utilizing a 2x2 factorial design (4 cells of  $n=10$ ,  $n=40$  total), to inform planning for a multi-center HIV/CVD polypill trial. We believe treatment with pravastatin (20mg daily) and lisinopril (10mg daily) will be well tolerated and be well adhered to by participants engaged in care and already adherent to ART. We hypothesize that Framingham risk score will improve with either drug intervention. Future sample size estimates will be generated from effect size related to changes in arterial elasticity and biomarkers.

**Primary Analyses:** Mean changes in FRS after 4 months will be studied with pravastatin use (versus placebo) and lisinopril use (versus placebo). The effect of both drugs combined, compared with double-placebo, will also be examined. Adherence and the frequency of intolerability, based on subjective or lab criteria, will also be compared between groups using the definitions listed in ‘outcomes’ (2.2). Elevations in lab values will also be categorized by severity (using established grades 1-4).

**Secondary Analyses:** Mean changes in hsCRP, IL-6, D-dimer, SAE, ApoB, ApoA1, and LDL and HDL particle concentrations will be studied after 4 months of pravastatin and lisinopril, given alone or in combination, using similar methods as above in primary analyses. Tests for correlation between change in these markers and BP, total cholesterol and FRS will also be considered. Regression models may be

considered to adjust for additional clinical characteristics (including, but not limited to traditional CVD risk factors), but power will be quite limited for these analyses.

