## 2.5. Sample Size Considerations

With a total sample size of 40 patients (20 per group for comparison of each drug intervention), a  $0.9 \times SD$  (standard deviation) difference in 10-year Framingham risk score from each drug can be detected with 80% power at the 0.05 (2-sided) level of significance. The variability in Framingham risk score was estimated from the Multiple Risk Factor Intervention Trial (MRFIT), where the estimated SD based on 11,702 participants was 0.20, corresponding to a relative change of approximately 20%. Thus, a  $0.9 \times SD$  change in this pilot study would correspond to an 18% relative change in Framingham risk score over the follow up period. Thus a change in Framingham risk of 8% to 6.5% would be  $>18\%$  relative improvement. In this proposal, if a 40-year old male smoker with SPB of 130mmHg, TC of 190mg/dL,

HDLc 35mg/dL demonstrated a reduction in SBP of -5mmHg and TC of -20mg/dL, and no increase in HDLc, his 10-year Framingham risk score would have a 25% relative improvement (8% to 5%). This is a very reasonable estimate as a mean change in TC of -40mg/dL after 12 weeks of pravastatin treatment was reported among 86 HIV-infected participants, and patients in our HCMC clinic commonly have lipid profiles less favorable than this.

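### The primary Framingham score analysis is not committed to a model with both randomised drugs and the baseline score; a plain two-group comparison would give intervals up to about 10% too wide and cost up to about 6 points of power

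*Combined protocol and SAP*

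**What the plan says.** Section 4 (Analysis Plan) introduces the trial as "utilizing a 2x2 factorial design" with four cells of 10. It then gives the primary FRS analysis as "Mean changes in FRS after 4 months will be studied with pravastatin use (versus placebo) and lisinopril use (versus placebo"), and adds that the two drugs together will be compared with double placebo. It names no test, model or factor term.

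Section 2.5 sizes the comparison as "20 per group for comparison of each drug intervention", for a difference of 0.9 SD that "can be detected with 80% power at the 0.05 (2-sided) level of significance".

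Regression appears only under Secondary Analyses in section 4. It is optional, it is described as having little power, and its purpose is given as models "considered to adjust for additional clinical characteristics (including, but not limited to traditional CVD risk factors"). The other study drug and baseline FRS are not named there. The secondary outcomes are to be analysed by methods similar to the primary ones, so whatever is chosen for FRS carries over to small artery elasticity (SAE) and the biomarkers.

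Sections 1.2 and 4 both expect each drug to lower FRS.

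**The concern.** In each group of 20, half the participants also receive the other active drug, which the plan expects to work. Balanced allocation cancels that effect out of the difference in means. A two-sample standard error does not know this: it sees two subgroups of 10 with different means inside each arm and counts the gap as random variation. The interval is then wider than the design warrants, and the test is conservative in exactly the case the trial hypothesises, where both drugs work.

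Baseline FRS is scheduled for every participant (table in section 2.4). A change score subtracts it with a slope fixed at 1, whereas fitting the slope would usually give a smaller residual variance.

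At stake is the precision of a 40-person pilot. There is also a planning consequence, since section 4 intends to derive future sample sizes from effect sizes for elasticity and biomarkers. If SDs for those outcomes were taken from two-group comparisons, their variance would be inflated by the same mechanism.

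**Working it through.** **Inputs from the documents**
- 40 participants, 20 versus 20 for each drug (section 2.5); four cells of 10 (section 4); blocks of 4 and 8 (section 2.4).
- 80% power, two-sided 0.05, difference 0.9 SD (section 2.5).
- SD: "where the estimated SD based on 11,702 participants was 0.20, corresponding to a relative change of approximately 20"%. A difference of 0.9 x 0.20 = 0.18 "would correspond to an 18% relative change in Framingham risk score over the follow up period".

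**Assumptions not in the documents**
- The 0.20 is a within-cell SD of change. Section 2.5 does not say whether it is that or the SD of a single score.
- The other drug's effect, e, in within-cell SDs: 0, 0.45 or 0.9.
- The correlation rho between baseline and month-4 FRS: 0.5, 0.7 or 0.9, with equal variances at the two times.

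**Step 1. Reproduce the stated power.** With unit SD, the standard error of the difference is sqrt(2/20) = 0.316, and 0.9/0.316 = 2.846. The normal approximation gives Phi(2.846 - 1.960) = 81.2%. The noncentral t with 38 df gives 79.2%. The stated 80% reproduces as a simple 20-versus-20 calculation.

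**Step 2. Leave the other drug out.** Half of each arm is shifted by e, which adds e²/4 to the within-arm variance. With exactly 10 and 10 in each arm, the expected pooled variance is 1 + (40/38) x e²/4.
- e = 0.45: 1 + (40/38) x 0.0506 = 1.053, SD factor 1.026.
- e = 0.9: 1 + (40/38) x 0.2025 = 1.213, SD factor 1.101.

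The true standard error of the difference remains 0.316, because the other drug is balanced across the arms. Only the estimated standard error is inflated. Putting the inflated SD into a standard power formula therefore overstates the loss slightly, and simulation is the better guide. Results from 40,000 simulated balanced trials of 4 x 10, with additive effects:

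| Other drug's effect (SD) | Two-group power | Two-factor power | Ratio of standard errors | Two-group type I error |
|---|---|---|---|---|
| 0 | 79.1% | 79.1% | 1.000 | 5.1% |
| 0.45 | 78.3% | 79.7% | 1.027 | 4.5% |
| 0.9 | 73.0% | 79.2% | 1.102 | 3.1% |

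The exact power of the two-factor model (37 df) is 79.1% whatever the other drug does; the small differences in that column are simulation error.

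**Step 3. Add baseline FRS.** The variance of change is 2s²(1 - rho), and the residual variance after fitting baseline is s²(1 - rho²). The ratio is (1 + rho)/2. With both factors and baseline in the model (36 df), for a 0.9 SD effect:
- rho 0.5: SD factor sqrt(0.75) = 0.866, power 89.2%.
- rho 0.7: SD factor sqrt(0.85) = 0.922, power 85.2%.
- rho 0.9: SD factor sqrt(0.95) = 0.975, power 81.1%.

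**Step 4. If 0.20 is the SD of a single score.** The SD of change is then 0.20 x sqrt(2(1 - rho)), which is below 0.20 when rho exceeds 0.5 and above it otherwise. The percentages above would move accordingly.

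**The case against.** The strongest reply is that the plan never prescribes a two-sample test. The sentence in section 4 says which contrasts will be studied and fits a two-factor model equally well. Section 4 opens with the factorial design, and section 2.3 says that design allows each treatment to be evaluated separately. The 20 per group in section 2.5 is a sample-size statement. This stands: the fault is an analysis left open, with the two-group comparison as its natural but not mandatory reading.

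Three stronger readings are tempting, and the documents do not support them.
- **That the plan ignores baseline, leaving chance imbalance uncorrected.** The outcome is change from baseline, so baseline is already subtracted. What is missing is a fitted slope.
- **That the stated 80% power is lost.** That figure rests on a 20-versus-20 calculation with no covariate, so omitting baseline takes nothing from it. Omitting the other drug costs power only if the two-group test is used and the other drug works. Section 2.5 gives 0.9 SD as a detectable difference; its worked example combines blood pressure and cholesterol changes and gives no expected effect per drug.
- **That results could be falsely positive.** The error runs the other way: estimates are unbiased and the type I error falls.

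A further objection is that a main-effects model forces the combined effect to be the sum of the two main effects, although section 4 lists the combination as its own comparison. That is right, and the assumption should be declared. With four equal cells and no covariate, the sum of the two estimated main effects equals the difference between the combination and double-placebo cell means, so the point estimate is then the same. The two approaches part when cells become unequal or a covariate is added, and in the residual variance if there is an interaction.

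**Conclusion.** The point holds as an analysis left uncommitted where a better one is available at almost no cost. If the two-group comparison is used, the loss is 0 to about 6 points of power (79% down to 73%) and an interval 0 to about 10% too wide, as the other drug's effect runs from 0 to the 0.9 SD design value. Type I error falls to about 3% at the upper end. These figures assume 0.20 is a within-cell SD of change, effects are additive and the cells stay balanced. Adjusting for baseline is a separate, forgone gain of about 2 to 10 points for correlations from 0.9 down to 0.5, none of which the documents give. The issue does not bias the estimates or undermine the design, but it should be settled before the data are unblinded.

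**What to change.** In section 4, replace the primary FRS sentence with a stated model: a linear model for log FRS at month 4 with an indicator for pravastatin, an indicator for lisinopril, and baseline log FRS. Report each main effect with its 95% confidence interval. The log scale matches the relative-change scale of section 2.5.

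Use the same model for systolic blood pressure, total cholesterol, SAE and the biomarkers, each with its own baseline value.

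Estimate the combination versus double placebo as a cell contrast after adding the interaction term. If it is taken from the main-effects model instead, say that additivity is assumed.

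In section 2.5, say what the SD of 0.20 measures.

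The cost is a few sentences, slightly more analysis work, and two degrees of freedom in the main model (38 to 36), with one more where the interaction is fitted. No extra data or visits are needed.

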## **2.3. Design Justification**

### General Design:

A randomized trial design will control for both known and unknown confounders, and the 2X2 factorial design will allow separate evaluation of the treatment interventions. Visit frequency was chosen to evaluate short-term tolerability and risk factor changes in an efficient manner with this initial pilot phase. Other CVD risk factors, such as smoking, will not specifically be targeted in the context of study visits so as not to confound the effect of pravastatin and/or lisinopril.

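### As written, the primary FRS analysis is an unadjusted month-4 change; a baseline-adjusted repeated-measures model would estimate the same month-4 effect somewhat more precisely and keep participants who leave after month 1

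*Combined protocol and SAP*

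**What the plan says.** Section 4 (Analysis Plan, Primary Analyses) describes the FRS comparison in one sentence: "Mean changes in FRS after 4 months will be studied with pravastatin use (versus placebo) and lisinopril use (versus placebo"). It adds a comparison of both drugs with double placebo. No test, model, baseline covariate or handling of missing month-4 values is stated. Regression adjustment appears only under Secondary Analyses, as an option, and month-1 FRS is not mentioned.

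Section 2.4 says that "participants will present month 1 and month 4 for repeat study procedures", and its table schedules blood pressure, lipids and FRS at baseline, month 1 and month 4. Artery elasticity and biomarkers follow the same three visits. Section 2.2 lists the outcome as "Changes in Framingham risk score (FRS), including serum cholesterol levels and blood pressure", without a time point. Section 2.3 gives the reason for the schedule: "Visit frequency was chosen to evaluate short-term tolerability and risk factor changes in an efficient manner with this initial pilot phase".

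Section 2.5 sizes the trial: "With a total sample size of 40 patients (20 per group for comparison of each drug intervention"). Section 4 says that future sample sizes will rest on effect sizes for arterial elasticity and biomarkers, and that the secondary outcomes will be analysed much as the primary one.

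**The concern.** A comparison of unadjusted mean changes fixes the weight on the baseline value at one. Unless baseline and follow-up are almost perfectly correlated, that weight is too large and baseline noise is carried into the drug effect. Estimating the weight, as a baseline-adjusted model does, removes that noise and leaves the randomised month-4 effect as the target.

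A change to month 4 also cannot be computed for anyone without a month-4 value, even if that person has a month-1 FRS. Section 3.2 allows withdrawal at any time and lists stopping criteria that can be met at the month-1 visit, so such cases are foreseeable. With 10 participants per cell, each loss counts. The same weakness would pass to small artery elasticity (SAE) and the biomarkers, which are the stated basis for sizing the next trial.

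**Working it through.** **Inputs from the documents.** 20 versus 20 for each drug, detectable difference 0.9 SD, SD 0.20, two-sided 0.05, 80% power (section 2.5); four cells of 10 (section 4); FRS at baseline, month 1 and month 4 (section 2.4).

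**Assumptions, because the documents are silent.** Equal variance at each visit; the same correlation ρ between any two visits, taken as 0.5 to 0.9; the plan's SD is the SD of the change.

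**1. The plan's own figure.** The standardised effect is 0.9/√(2/20) = 2.846. The normal approximation gives Φ(2.846 − 1.960) = 81.2%; the noncentral t with 38 df gives 79.2%. The stated 80% reproduces.

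**2. Baseline adjustment at month 4.** In units of the FRS variance, the change score has variance 2(1 − ρ) and the baseline-adjusted month-4 value has 1 − ρ². The ratio is (1 + ρ)/2. Power is the noncentral t at 0.9 SD, with effect 0.9/√(ratio × 2/20).

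| ρ | Variance ratio | Cut | Power at 0.9 SD | SD difference with the plan's precision |
|---|---|---|---|---|
| 0.5 | 0.75 | 25% | 89% | 0.9 × √0.75 = 0.78 |
| 0.7 | 0.85 | 15% | 85% | 0.9 × √0.85 = 0.83 |
| 0.9 | 0.95 | 5% | 81% | 0.9 × √0.95 = 0.88 |

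The adjustment costs about one degree of freedom; using 36 df instead of 38 moves these powers by about 0.1 percentage point. Chance baseline imbalance also takes back a little precision, which matters most at ρ = 0.9, where the gain is smallest.

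**3. What month 1 adds to the month-4 contrast.** With complete data, essentially nothing. If a fraction m of month-4 values is missing at random, the further variance cut is about m × r², where r = ρ/(1 + ρ) is the correlation of months 1 and 4 given baseline.

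- ρ = 0.7: r² = (0.7/1.7)² = 0.170, so 1.7% at m = 10% and 3.4% at m = 20%.
- ρ = 0.5: r² = 0.111, so 1.1% and 2.2%.
- ρ = 0.9: r² = 0.224, so 2.2% and 4.5%.

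That is roughly 2–4%. A simulation with 10 per cell, ρ = 0.7 and 15% missing month 4 agrees. The standard error of the log-FRS effect was about 0.070 for the change score, 0.065 for baseline-adjusted month 4, and 0.064 with month 1 added.

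**4. The average of months 1 and 4.** Its baseline-adjusted variance is (1 + ρ)/2 − ρ². Relative to the planned change score this is 0.50, 0.60 and 0.70 at ρ = 0.5, 0.7 and 0.9; relative to adjusted month 4 it is 0.67, 0.71 and 0.74. If the month-1 effect is a fraction f of the month-4 effect, the average estimates (1 + f)/2 of it. It has more power than adjusted month 4 only if f exceeds 2√(0.67) − 1 = 0.63, 0.68 or 0.72 respectively. At f = 0.6 its power is 82% at ρ = 0.7, against 85% for adjusted month 4. At ρ = 0.9 it is 75%, below the plan's own 79%.

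**The case against.** The month-4 change is a legitimate end-of-treatment target for a 40-person pilot, and the plan's power statement is correct for it. This stands, and it is why month 4 should remain the primary contrast. It does not argue for the unadjusted form, since adjustment leaves the target unchanged.

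A reader might infer that ignoring month 1 throws away a large, free gain, with power rising from 79% to about 95% (ρ = 0.7). The documents do not support that. The figure combines baseline adjustment, a switch to the average over visits, equal correlations and an equal drug effect at month 1; the last two are nowhere stated. If the two on-treatment values are more alike, say correlated at 0.85 with each 0.7 with baseline, averaging cuts variance by 15% relative to adjusted month 4, not 29%. Likewise, a fall in standard error from 0.070 to about 0.052 compares two different estimands.

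A reader might also infer that averaged FRS should be the planning estimate. Section 4 bases future sample sizes on arterial elasticity and biomarkers instead.

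Finally, the plan does not say that participants without a month-4 visit will be excluded. It gives no rule, and the 10–20% missing used above is an assumption. The criticism is that the rule is missing, not that a wrong one was chosen.

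**Conclusion.** The point holds in a limited form. As written, the primary FRS comparison uses neither baseline adjustment nor the month-1 values, and a better method exists for the same estimand with data already collected. Baseline adjustment supplies most of the gain: 25% to 5% less variance for each month-4 effect, and power of 89% to 81% instead of 79%, over an assumed equal correlation of 0.5 to 0.9. At the upper end the gain is slight. Month-1 values contribute little precision to the month-4 effect; their value is to keep participants lost after month 1 in the analysis. The larger gains from averaging the two visits belong to a different question and depend on a month-1 effect that the documents do not give. The stated sample size is not in error.

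**What to change.** In section 4, replace the mean-change sentence with a repeated-measures model:

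- **Outcome and covariates:** FRS at months 1 and 4, with terms for baseline FRS, visit, pravastatin, lisinopril and each drug by visit.
- **Population:** all participants with any follow-up FRS, by assigned group.
- **Primary contrast:** the month-4 effect of each drug, the same estimand as now.
- **Combination versus double placebo:** estimate it from the four cells or by adding a drug-by-drug term. Without that, the model would give only the sum of two separate effects.
- **Supportive only:** the average of months 1 and 4, labelled as a different estimand that is diluted if the month-1 effect is smaller.
- **SAE and biomarkers:** use the same model, since they are also measured at month 1 and are the stated basis for future sample sizes.

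The cost is analysis-plan wording, slightly more programming and about one degree of freedom. No extra visits, samples or participants are needed.
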